#### Lever Positioning Manipulation (LPM)

LPM Treatment [26]: All LPM treatments were conducted by the same rehabilitation expert, [name], who has 33 years of experience in the field. The specific LPM procedure entailed positioning the patient with flexed knees and hips, crossing the lower limbs. The practitioner pinpointed the site of the lumbar disc herniation, using their right elbow to stabilize at this point while holding the patient's ankles with both hands. Utilizing the principle of leveraged force, the practitioner lifted and pulled the patient’s lower limbs upwards and inwards to just before the point of hyperextension. Upon reaching the trigger point, the practitioner executed a rapid pull with the lever, feeling for a 'click' or loosening at the herniation site, at an angle of approximately 5°. During this lever maneuvering and pulling, the patient was instructed to exhale (Fig. 2).

**Fig. 2 Fig2:**
[figure not shown]
Lever positioning manipulation (LPM) operation diagram: **A** Massaging and manipulation for lumbar muscular relaxation. **B** LPM

Sham-LPM Treatment: All preparatory steps, patient positioning, and the duration before the commencement of Sham-LPM were identical to those of the LPM treatment, thus effectively minimizing operational bias. The key difference in sham-LPM is that when the patient's position reaches the critical point, the operator does not perform a swift twisting motion. Instead, a protective belt is used to maintain the patient’s position unchanged (Fig. 2).

#### Multimodal fMRI and MRS Scan

Participants in this study were recruited and evaluated at the Massage Department of the Third Affiliated Hospital of Zhejiang Chinese Medical University. Those who met the inclusion criteria underwent data collection using a Siemens Skyra 3.0 T superconducting MRI scanner at Zhejiang Hospital (MAGNETOM Skyra 3.0 T, Siemens, Germany). To minimize confounding factors, clinical interventions for patients with LDH were consistently performed at Zhejiang Hospital, with MRI data collection taking place within 1 h of completing the intervention.

For the LDH group, multimodal fMRI and MRS scans were conducted both before and after immediate treatment. Conversely, the healthy control group underwent a single session of multimodal fMRI and MRS scanning at the time of their enrollment. It is common for patients to experience more pronounced pain sensations on the day of their medical consultation. Hence, to ensure the timely acquisition and reliability of brain function data in response to pain stimuli, MRI scans were conducted on all study participants on the same day they were enrolled and had completed their baseline data assessment.

For structural imaging, a Gradient echo sequence 3D-T1 will be utilized with the following parameters: 249 slices, repetition time (TR) of 2530 ms, echo time (TE) of 2.89 ms, slice thickness of 1.2 mm, layer spacing of 1.0 mm, voxel size of 1 mm × 1 mm × 1 mm, flip angle of 9°, field of view (FOV) of 256 mm × 256 mm, and a data matrix of 64 × 64. The duration of the 3D-T1 sequence will be approximately 5 min and 53 s.

FMRI scans will be acquired using an echo-planar imaging sequence with these settings: 43 slices, TR of 2680 ms, TE of 30 ms, slice thickness of 3.0 mm, no gap, voxel size of 3 mm × 3 mm × 3 mm, flip angle of 9°, FOV of 192 mm × 192 mm, and a data matrix of 64 × 64. The functional sequence will take about 10 min and 53 s.

MRS scans will be conducted using a PRESS (Point-Resolved Spectroscopy) sequence with these parameters: TR of 1700 ms, TE of 35 ms, slice thickness of 2.0 mm, no gap, voxel size of 10 mm × 10 mm × 10 mm, FOV of 240 mm × 240 mm, and a data matrix of 128 × 128. The PRESS sequence will take approximately 9 min and 13 s.

#### Multimodal fMRI and MRS processing

In this study, we enhanced and streamlined data preprocessing using the Graph Theoretical Network Analysis Toolbox (GRETNA-master; [
https://www.nitrc.org/frs/downloadlink.php/10441](https://www.nitrc.org/frs/downloadlink.php/10441.)) within Matlab 2013b (Mathworks, Natick, MA, USA). The first step involved converting raw fMRI data into a format compatible with both GRETNA and SPM12 (SPM12; [http://www.fil.ion.ucl.ac.uk/spm/software/spm12/](http://www.fil.ion.ucl.ac.uk/spm/software/spm12/)). To ensure signal consistency and ease participant adaptation, the first ten temporal points of the data were excluded.

Subsequently, we carried out a detailed temporal correction to synchronize the time series across all slices. This was followed by a precise correction for head movement, using a six-parameter rigid-body transformation to counteract any participant movement during the scan.

For image registration, resting-state fMRI (rs-fMRI) scans were co-registered with high-resolution anatomical 3D-T1 scans. These scans were then spatially normalized to align with the Montreal Neurological Institute (MNI) template. This step involved using Diffeomorphic Anatomical Registration Through Exponentiated Lie Algebra (DARTEL) for advanced non-linear warping of the 3D-T1 images, and then applying the same normalization parameters to the rs-fMRI scans.

Spatial smoothing was performed by applying a Gaussian kernel with a 3 mm full-width at half maximum to the normalized scans, reducing spatial noise and enhancing signal quality. We ensured that spatial movements and rotations were restricted to less than 1.5 mm and 1.5° in any direction to maintain data integrity.

Lastly, the data underwent detrending and filtering. Detrending, aimed at removing noise factors such as scanner heating, was conducted using linear regression. Filtering was implemented because the Blood Oxygenation Level-dependent (BOLD) signal, generated by spontaneous neuronal activity in the resting state, is predominantly concentrated in the low-frequency range. Thus, high-frequency signals like those from breathing and heartbeats were filtered out, while also avoiding low-frequency drift. The frequency band used in this study was 0.01–0.08 Hz.

#### Calculation of fMRI and MRS

FMRI images, prior to filtering, were transformed into the frequency domain using a fast Fourier transform to obtain the power spectrum. The square root of the power spectrum was averaged across the 0.01–0.08 Hz frequency range at each voxel, and these average values were recorded as the ALFF. To standardize the ALFF for subsequent statistical analysis, the ALFF of each voxel was divided by the global mean ALFF value.

For the calculation of ReHo, data without smoothing were utilized. ReHo was computed through Kendall’s Coefficient of Concordance (KCC) to assess the synchronization of the time series of a given voxel with its 26 nearest neighboring voxels. Individual ReHo maps were then standardized by dividing them by the global mean ReHo value and subsequently smoothed with a Gaussian kernel of 6-mm full width at half maximum.

Brain regions showing statistically significant differences in ALFF and ReHo values were identified as the ROIs for further analysis of brain network FC. FC provides a macroscopic view of the connectivity within the entire brain's functional network and is valuable for identifying neuroimaging markers for LDH.

The results of each independent component in the experiment included a correlated activation time series and an independent 3D spatial distribution of brain voxel images. For this analysis, we used the Group ICA of fMRI Toolbox (GIFT) software (version 3.0, [http://mialab.mm.org/software/gift/](http://mialab.mm.org/software/gift/)) to perform spatial independent component analysis. The component data of the participants were estimated using the algorithm of maximum entropy. The ICASSO method ([http://research.ics.tkk.fi/ica/icasso](http://research.ics.tkk.fi/ica/icasso)), with 30 repeated computations, facilitated the clustering analysis of the final component results, thereby determining the reliability of the component estimation.

^1^H-MRS is used to measure the concentrations of NAA, Cho, Cr and phosphocreatine, and to estimate the concentrations of neurotransmitters such as glutamic acid, glutamine and GABA in the brain. ^31^P-MRS was used to detect adenosine triphosphate, phosphodiester, phosphomonoester, phosphocreatine, and inorganic phosphoric acid, and to estimate brain pH. MR Analysis software was used to automatically analyze the spectral signals and measure the metabolites. MRS Mainly focused on hydrogen proton (^1^H) and phosphorus (^31^P).

#### Image viewing

For the visualization of statistical results, we will utilize the xjview 95 toolkit ([https://www.alivelearn.net/xjview/xjview-9-5-released/](https://www.alivelearn.net/xjview/xjview-9-5-released/)), which will employ the Montreal Neurological Institute (MNI) system for coordinate localization and the Anatomical Automatic Labeling (AAL) 90 atlas for brain region labeling. To create a three-dimensional map of the entire brain, the BrainNet Viewer toolkit will be employed.

Brain regions that will display statistically significant differences will be identified based on specific criteria: a cluster volume threshold (cluster) of ≥ 50 voxels and a single voxel threshold of *P* < 0.005. Additionally, to minimize the likelihood of Type I errors, a False Discovery Rate (FDR) correction (Glickman et al., 2014) will be applied with a threshold of *P* < 0.05. These stringent criteria and visualization tools will facilitate the precise identification and graphical representation of areas of the brain significantly impacted in the study.

### Patient safety

Patient safety measures will include the routine examination of blood, urine, and stools; blood biochemical testing (including liver and kidney function); and electrocardiography, which will be performed for each participant before trial enrollment. Any adverse events caused by LPM will be reported to the project leader, the research institute, and the ethics committee within 24 h and will be documented in the case report form (CRF).

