**Methods and analysis:**

A total of 60 LDH patients and 30 healthy controls, matched by gender, age, and years of education, will be enrolled in this study. The LDH patients will be divided into two groups (Group 1, *n* = 30; Group 2, *n* = 30) using a random number table method. Group 1 will receive LPM treatment once every two days, for a total of 12 times over 4 weeks. Group 2 will receive sham LPM treatment during the same period as Group 1. All 30 healthy controls will be divided into Group 3. Multimodal MRI will be performed on Group 1 and Group 2 at three time points (TPs): before LPM (TP1), after one LPM session (TP2), and after a full course of LPM treatment. The healthy controls (Group 3) will not undergo LPM and will be subject to only a single multimodal MRI scan. Participants in both Group 1 and Group 2 will be required to complete clinical questionnaires. These assessments will focus on pain intensity and functional disorders, using the Visual Analog Scale (VAS) and the Japanese Orthopaedic Association (JOA) scoring systems, respectively.

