### Participants

Sixty patients with LDH and thirty with HCs will be recruited for this study. All 60 LDH patients were randomly divided into 2 groups with 30 patients in each group. The Group1 will be treated with LPM and Group2 will be treated with sham LPM.

Inclusion criteria for the LDH patients are as follows: participants must meet the diagnostic criteria for lumbar disc herniation, including protrusion types such as central, paracentral, far lateral, foraminal, and subarticular, with imaging findings that align with neurological localization. The age range for participants is 18 to 65 years, encompassing any gender, and they must be right-handed. Participants should be in the non-acute phase of the condition, experiencing mild to moderate pain and functional impairment, with the duration of symptoms exceeding 2 weeks. They should have a Visual Analog Scale (VAS) score greater than 4 and Japanese Orthopaedic Association (JOA) scores less than 15 [26]. Eligible participants must not have taken analgesics, neurotropic nutrition drugs, or sedatives in the past month and should not have undergone systemic treatment. Additionally, they should not have received spinal manipulation or other physical therapies in the past month. Finally, participants must voluntarily agree to participate in this study and have signed an informed consent form.

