### Randomization, allocation concealment, and blinding

After baseline assessments, eligible participants with LDH will be randomly allocated to either the LPM group or the sham-LPM group through a randomization process. A random number grouping table will be generated based on the predetermined number of cases and a specified random proportion. These randomization tables will be created using SAS 9.0 software and will be managed by independent research assistants who are not involved in the participant recruitment, assessment, or intervention processes.

Independent research assistants will inform eligible participants of their group assignment results via phone communication. Due to the nature of the interventions, it is not possible to implement blinding for researchers, participants, and practitioners throughout the course of the experiment. However, laboratory technicians and researchers responsible for conducting statistical analyses will be kept blinded to group assignments to ensure the objectivity and integrity of the data analysis.

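### Adverse-event reporting and CRF recording depend on an event being attributed to LPM, so the counts could not support a fair LPM-versus-sham description of harm

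*Protocol article*

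**What the plan says.** The Patient safety section has two parts. The first lists laboratory tests and electrocardiography, "which will be performed for each participant before trial enrollment". The second is the adverse-event rule: "Any adverse events caused by LPM will be reported to the project leader, the research institute, and the ethics committee within 24 h". The same sentence continues "and will be documented in the case report form (CRF"). It therefore has one subject, events attributed to LPM, and two consequences: expedited reporting and entry in the CRF.

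The trial has a randomised sham arm. The Participants section says "All 60 LDH patients were randomly divided into 2 groups with 30 patients in each group" and "The Group1 will be treated with LPM and Group2 will be treated with sham LPM". The abstract adds that "Group 2 will receive sham LPM treatment during the same period as Group 1". The sham description says "All preparatory steps, patient positioning, and the duration before the commencement of Sham-LPM were identical to those of the LPM treatment"; sham differs in that the final rapid movement is left out and a belt holds the patient in position.

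The section on randomization, allocation concealment and blinding says "it is not possible to implement blinding for researchers, participants, and practitioners throughout the course of the experiment". Only laboratory technicians and the statistical analysts are to be kept blinded.

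**The concern.** A randomised sham arm lets one judge whether events on the active treatment exceed the background, without deciding the cause of each event. That works only if events are collected in both arms in the same way and before anyone judges cause. Here the causality judgement comes first and decides whether an event is written down at all.

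Three features of the design make this matter:

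- In this population, pain or neurological worsening can come from the disc disease or from the procedure, so attribution of a single case is uncertain.
- Sham patients go through the same preparation and positioning, so they can have procedure-related events too.
- Those most likely to judge cause know which procedure was given.

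At stake is any statement about the safety of LPM drawn from this trial, even a simple table of events by group. An event that was never entered may not be recoverable afterwards.

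**Working it through.** The article gives no figure for adverse events: no expected rate, no safety sample size and no planned test. There is nothing to reproduce, so the check is one of reading, followed by a short illustration.

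**Step 1: is there any other rule?** The adverse-event sentence in Patient safety is the only one in the text. The tests and electrocardiogram in that section are stated for the period before enrolment, so no described on-treatment safety examination would pick up what the rule misses. The Procedure section collects VAS and JOA in both patient groups at two time points, but as outcome scores. The trial schedule (Fig. 1) is not shown in the text at hand and could not be checked.

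**Step 2: what does the rule cover?** Two readings are possible.

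| Reading | Group 1 (LPM, 30) | Group 2 (sham, 30) |
|---|---|---|
| A. LPM means the active manipulation | recorded if attributed to LPM | outside the rule |
| B. LPM means either study procedure | recorded if attributed to the procedure | recorded if attributed to the procedure |

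Reading A leaves out 30 / 60 = 50% of the randomised patients. Reading B leaves out no group, but keeps the attribution filter in both.

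**Step 3: what does the filter do to a comparison?** Let p1 and p2 be the true proportions of patients with an event on LPM and sham, and a1 and a2 the fractions of those events attributed to the procedure and so recorded. The expected recorded counts are 30·p1·a1 and 30·p2·a2, and their ratio is

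(p1 / p2) × (a1 / a2).

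The recorded ratio equals the true ratio only if a1 = a2. With attribution probably made by people who know the arm, nothing in the plan secures that equality.

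**Step 4: illustration, with assumed rates.** Take equal true rates in both arms, so the correct ratio is 1.

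| Assumed p, both arms | True expected events per arm (30·p) | Recorded if all are attributed | Recorded if half are attributed |
|---|---|---|---|
| 5% | 1.5 | 1.5 | 0.75 |
| 10% | 3 | 3 | 1.5 |
| 20% | 6 | 6 | 3 |
| 30% | 9 | 9 | 4.5 |

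Under reading B, with all events attributed on LPM and half on sham, the recorded ratio is 1 / 0.5 = 2 although the arms do not differ. With the fractions reversed it is 0.5 / 1 = 0.5. Under reading A, the second column is also the expected number of sham events that the rule does not call for. The bias can make LPM look worse or better than it is. The rates and fractions are assumptions. The conclusion needs only that attribution decides recording and may differ by arm.

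**The case against.** The best case on the other side has four parts.

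- **The sentence does not say only.** It does not forbid recording other events. The source is an article that condenses a fuller protocol, and neither that protocol nor the CRF is shown. This stands as a limit: a reader might infer that sham events and unattributed events are certainly lost, and the article does not establish that. It does not remove the point, because the article is not silent. It states a recording rule and ties it to attribution. If the CRF captures more, the published sentence misdescribes it and should still be corrected.
- **LPM is used loosely.** The abstract and the Procedure section describe the scan times of both patient groups by reference to LPM, although Group 2 receives sham. The exclusion of the sham arm is therefore the literal reading and not a certainty. Reading B keeps the attribution filter, so the point survives in narrower form.
- **No stated analysis is broken.** The aim is mechanistic, no safety endpoint or harm comparison is planned, and the Discussion rests the safety of LPM on earlier cited work. This stands. Marked worsening of pain or function would also show in VAS and JOA in both arms, although not as an adverse event and not between the two assessments.
- **Who judges cause is not stated.** Unblinded attribution is probable from the blinding section, but it is an inference.

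**Conclusion.** The point holds in a limited form. The article makes both the 24 h report and CRF entry depend on attribution to LPM and gives no rule for events regardless of cause. On the literal reading, 30 of the 60 randomised patients are outside the rule. On the looser reading all 60 are inside it, but recording still passes through a causality judgement that is probably unblinded. On either reading, the resulting counts could not support a fair description of harm on LPM against sham.

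This rests on two assumptions: that the sentence describes what sites will do, and that no unseen form or schedule overrides it. It does not show that the trial will lose events, and it does not touch the imaging or VAS/JOA results. The defect is worth correcting because the remedy is cheap and events missed during treatment may not be recoverable.

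**What to change.** Replace the adverse-event sentence in Patient safety with a rule that separates recording from attribution:

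- All adverse events in Group 1 and Group 2, whatever the suspected cause, are recorded in the CRF.
- Patients in both groups are asked about events in the same way and on the same schedule.
- Recording runs from the first session through the last study contact, including events reported after the TP3 scan. Stopping at TP3 would be too early, since that scan falls within one hour of the last session.
- Causality is entered as a separate item.
- Events are tabulated by randomised arm.
- The existing 24 h report applies to both arms on the same terms.

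If the full protocol and CRF already work this way, only the article's sentence needs correcting. Otherwise the cost is a short amendment, a change to the CRF wording and a little extra recording by existing staff. No treatment, scan or outcome assessment changes.

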## Discussion

The clinical effectiveness and safety of LPM intervention for LDH have been validated on multiple occasions [11, 12], yet the mechanisms underlying its analgesic effects remain to be elucidated. Most researchers concur that the brain plays a central role in these analgesic effects [13–16]. Multimodal fMRI and MRS techniques allow for a non-invasive direct study of the mechanisms of analgesic effects in the human brain from both qualitative functional and quantitative metabolic dimensions. Numerous studies have demonstrated that combining these two techniques enhances the credibility of research outcomes [27–33].

In our preliminary experiments [26], we observed extensive and immediate activation of brain regions following LPM intervention for LDH, suggesting a central and networked regulation. To further explore the regulatory mechanisms of key brain regions responsible for the analgesic effects and to identify the critical neurotransmitters involved, this study employs multimodal fMRI and MRS techniques. It will analyze brain functional metrics such as ALFF, ReHo, and FC, as well as detect signals related to brain metabolites and neurotransmitters like NAA, Cho, and GABA. The ultimate goal is to elucidate the core neurobiological mechanisms by which LPM intervention for LDH exerts its clinical analgesic brain effects.

## Data Availability

No datasets were generated or analysed during the current study.

## Abbreviations

LDH: Lumbar disc herniation
LPM: Lever positioning manipulation
fMRI: Functional magnetic resonance imaging
MRS: Magnetic resonance spectroscopy
ALFF: Amplitude of low-frequency fluctuation
ReHo: Regional homogeneity
NAA: N-acetylaspartate
Cho: Choline
Cr: Creatine
Glu: Glutamate
Gln: Glutamine
GABA: Gamma-aminobutyric acid
ROI: Regions of interest
JOA: Japanese Orthopaedic Association
VAS: Visual analog scale
KCC: Kendall's coefficient of concordance
FDR: False discovery rate
HCs: Healthy controls
TPs: Time points
MNI: Montreal Neurological Institute
TR: Repetition time
TE: Echo time
FOV: Field of view
CRF: Case report form
